## Abstract

**Background:**

Catheter ablation for atrial fibrillation is recommended for symptomatic patients after failed medical therapy. Ablation has a higher failure rate in obese patients, and both the prevalence of atrial fibrillation and obesity are increasingly globally. The outcome of ablation can be improved if obese patients can achieve goal-oriented weight reduction prior to ablation. Conventional weight loss strategies, however, can be difficult to access and can delay ablation, thereby risking a lower chance of maintaining sinus rhythm. Effective weight-loss medications, such as the glucagon-like peptide inhibitor-1 drugs, offer the potential for incremental impact on weight loss over a shorter period of time as a bridging therapy. The aim of this study is to assess the feasibility of using liraglutide, a glucagon-like peptide inhibitor-1, in producing weight loss in obese patients before catheter ablation.

**Methods:**

The study is an open-label, uncontrolled, prospective single-centre feasibility study of daily liraglutide injections in the treatment of obese patients for at least 13 weeks before and 52 weeks after AF ablation. Adult patients with symptomatic AF whose body mass index ≥ 30 will be recruited from those planning to undergo ablation. Feasibility will be determined based on the recruitment rate, adherence to the medication, and the amount of weight loss achieved over the study period. Exploratory outcomes include changes in atrial structure, function, and fibrosis with weight loss evaluated by cardiac magnetic resonance imaging, electroanatomic mapping, and patient-reported outcome measure.

**Discussion:**

This study will allow us to determine whether the use of liraglutide in obese patients with atrial fibrillation undergoing ablation is feasible with adequate recruitment. The additional information on adherence and average weight loss over the study period will inform the design of a future definitive randomized controlled trial.

**Trial registration:**

ClinicalTrials.gov (NCT05221229). Registered on 2 February 2022.

**Supplementary Information:**

The online version contains supplementary material available at 10.1186/s40814-024-01454-y.

## Background

Atrial fibrillation (AF) is the most common arrhythmia in clinical practice, and the prevalence is expected to rise worldwide. AF increases the risk of hospital admissions, stroke, dementia, and mortality, and it lowers quality of life (QoL). The prevalence of obesity has tripled since 1975 [1] and is increasingly recognized as a stand-alone risk factor for AF independent of associated conditions such as hypertension, diabetes mellitus, and obstructive sleep apnoea [2–4]. The risk of developing AF [5], likelihood of progression [6], and a poor response to its management [7, 8] are all increased with progressive weight gain. Rhythm control therapies such as direct current cardioversion, antiarrhythmic drugs, and catheter ablation are important treatments of AF in maintaining sinus rhythm, improving symptoms and QoL, and reducing repeated hospitalization [9]. Cather ablation is, however, the most effective rhythm control therapy for symptomatic AF patients unresponsive to medications [10–13]. Accumulating evidence suggests that rhythm control management should be considered as early as within 1 year of AF diagnosis [14–17]. However, obesity (body mass index, BMI ≥ 30) lowers the success rate of ablation by up to 10% [18]. Multiple studies have reported that goal-directed weight reduction and optimization of risk factors can reduce AF progression, improve both single and multi-procedure success rates following ablation, and long-term maintenance of sinus rhythm [19–22].

In clinical practice, conventional weight loss strategies such as intensive lifestyle modification, pharmacotherapy such as orlistat, and bariatric surgery have limitations. These include limited availability across all healthcare systems, poor tolerability, invasive nature, and delay in achieving the required weight loss. As a result, an alternative or bridge therapy for this cohort should be explored. The newer weight loss medications such as liraglutide and semaglutide have potentials to close this gap [23, 24]. In this study, liraglutide was selected in preference to semaglutide due to its long-term safety [25].

The primary outcome for a future definitive randomized controlled trial comparing goal-oriented weight reduction with liraglutide together with risk factor modification group to risk factor modification alone will be the effect on AF-free survival at 52 weeks following AF ablation. Such a study cannot be adequately designed without evidence that liraglutide can achieve weight loss in this cohort between identification of the need for ablation and the procedure (on average 13 weeks), that adherence is maintained before and after ablation, and that recruitment rates are sufficient. This knowledge is essential to design a future definitive trial.

### Aims and objectives

The primary aim of this feasibility study is to determine whether liraglutide injected 3 mg once daily for 13 weeks before first-time AF ablation and continued for 52 weeks after ablation is a feasible method of reducing the recurrence and burden of AF (reported as percentage of total recordings) detected by Kardia portable electrocardiogram (ECG) recordings (at least twice a day and according to symptom-triggered recordings) after catheter ablation in patients with paroxysmal or persistent AF and body mass index above 30. In our centre (Queen Elizabeth Hospital, Birmingham, QEHB), the usual waiting time for patients for their first-time ablation is at least 12 weeks. A shorter waiting time is unusual in the United Kingdom (UK), and a longer waiting time needs to be avoided, as delay increases risk of AF recurrence.

Feasibility (the primary objectives) of the study will be determined by the measurement of the following:The number of participants recruited as a proportion of those eligible for the study over the recruitment periodThe proportion of participants adherent to liraglutide until the end of 52 weeks follow-up after ablationThe percentage of weight loss (from recruitment) achieved at the time of ablation and the end of follow-up period after ablation.

Exploratory outcomes will also be determined as follows:The proportion of participants adherent to Kardia recording requirements (at least twice daily recordings over 52 weeks)The time-to-first recurrence of AF (> 30 s) beyond 12-week blanking period post ablationThe burden of AF (percentage of total observed time) beyond 12-week blanking period post ablation in predefined periods (13th–26th weeks, 27th–39th weeks, and 40th–52nd weeks following ablation)Changes in cardiac MRI (CMR) measures from baseline to before ablation◦ Epicardial adiposity (volume measure in cm^3^)◦ Left atrial fibrosis (percentage of scar to total atrial volume rendered in CEMERGAPP by using late gadolinium-enhanced left atrial CMR images)Changes in fibroblast growth factor (FGF)-23 (pg/ml) and bone morphogenic protein (BMP)-10 (ng/ml) levels from baseline to before ablationChanges in electro-anatomic mapping data (right atrial bipolar voltage [mV] and conduction velocity [cm/s]), from baseline to before ablation

## Methods and design

### Study design and population

This is an open-label, uncontrolled, prospective, single-centre feasibility study of liraglutide in the treatment of obese AF patients injected for at least 13 weeks before and 52 weeks after AF ablation. Patients waiting for first-time AF ablation in QEHB will be invited for the study. We aim to recruit 30 patients who meet the eligibility criteria. Potential participants will be screened through cardiology outpatient clinics and the waiting list for AF ablation at QEHB.

#### Inclusion criteria

Adult patients with paroxysmal or persistent AF (> 18 years of age)Symptomatic: Defined as palpitations, shortness of breath, and feeling of an irregular pulse or pause in heart activity, despite guideline-directed medical therapy (or inability to take medications)Body mass index above 30 kg/m^2^ (Mosteller equation)

#### Exclusion criteria

A contra-indication or caution to treatment with liraglutide or to any study procedure, including CMRPrevious or current use of medication or planned surgery for weight lossType 1 diabetesType 2 diabetes on DPP-IV inhibitor or insulin

### Study setting, patient identification, and recruitment

QEHB is the main tertiary referral centre for AF ablation in Birmingham, the second largest city in the UK with a population of 1.1 million [26]. All the research will take place in QEHB. The study is supported by the cardiology research group and electrophysiology team. No additional screening, including laboratory and diagnostic testing, is required to meet the inclusion and exclusion criteria of the study. Eligible participants will be screened through cardiology outpatients’ clinics and the waiting list for AF ablation run by the electrophysiology consultants. Identified patients will be approached by members of the clinical team and, if interested, will be given a patient information sheet (PIS) to facilitate the consenting process. All participants who are eligible into the study will then go through a formal consent process with one of the research team members, according to good clinical practice guidelines. During the process, adequate time will be given to the potential participants to decide whether to take part in the study. Patients who are currently participating in other research projects will not be recruited.

### Justification of sample size

Feasibility studies are not designed to prove the superiority of one treatment over another. Instead, the aim is to test whether the proposed intervention is a feasible method of treatment in this group of patients. Our internal unpublished data suggests QEHB performs first-time AF ablation on approximately 140 patients per calendar year, and 40% (56) of patients will be eligible for inclusion. We aim to recruit 30 patients in total by assuming just over 50% of eligible patients will agree to participate with an approx. 10% dropout rate. We expect 70% (21) of recruited participants to remain adherent to liraglutide at the end of the study based on previous published data [23]. Using the binomial exact method for this proportion results in the 95% confidence interval being 15–25 recruited participants to remain adherent to liraglutide at 52 weeks following ablation. As there is no current study recruiting similar patients, the investigators expect to complete recruitment within 52 weeks.

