### Feasibility outcome measures

The study will be considered feasible if as follows:Recruitment rate ≥ 50% (≥ 30 patients) of those eligible (56 patients per year), drop-out rate < 10%, and data completeness ≥ 90%Adherence to medication rate ≥ 70% in the participants at the end of study [23]. Adherence will be measured by the proportion of patients who tolerate total cumulative dose of 657 mg and more of liraglutide at 1 year (minimal maintenance dose of 1.8 mg over 365 days).Weigh loss at least 5% from baseline in ≥ 60% participants at the end of study [23, 27]. Body mass change in kilograms and BMI between the baseline, at ablation, and last days of treatment with liraglutide (± 7 days) will be measured using a single set of calibrated scales using a standardized protocol.

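### The drop-out cut-off for feasibility (below 10%) excludes the drop-out the plan expects (about 10%), and the recruitment and adherence cut-offs sit at their planned values with no intermediate outcome

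*Protocol article*

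**What the plan says.** All references are to the protocol article.

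**Planning values (Justification of sample size).** The centre treats "approximately 140 patients per calendar year, and 40% (56) of patients will be eligible for inclusion". The target follows from this: "We aim to recruit 30 patients in total by assuming just over 50% of eligible patients will agree to participate". The same sentence carries the drop-out allowance, since these patients "will agree to participate with an approx. 10% dropout rate". On adherence: "We expect 70% (21) of recruited participants to remain adherent to liraglutide at the end of the study". The precision given for that figure is a "95% confidence interval being 15–25 recruited participants to remain adherent to liraglutide".

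**Decision rule (Feasibility outcome measures).** One statement lists the conditions under which the study counts as feasible:
- The first item joins three conditions: recruitment of at least 50%, glossed as at least 30 patients, "of those eligible (56 patients per year), drop-out rate" strictly below 10%, and data completeness of at least 90%.
- The second item requires an "Adherence to medication rate" of at least 70%.
- The third requires at least 5% weight loss in at least 60% of participants.

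The section gives no tolerance, no intermediate outcome and no rule for a criterion that is narrowly missed.

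**The concern.** The planning paragraph and the decision rule give drop-out figures that cannot both stand. With 30 recruited, 10% is 3 patients, and 3 of 30 is not below 10%. The outcome the investigators plan for is one that their rule classes as not feasible.

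Two further cut-offs, recruitment and adherence, equal the planned values. They are inclusive, so they pass if the result lands exactly on plan. But a cut-off placed at the expected value and judged on a point estimate from 30 patients is missed in something close to half of studies, even when the planning assumption is true.

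The feasibility verdict is a main product of this study, and the Background and the abstract's Discussion make it the basis for designing a definitive randomised trial. A rule that tends to say not feasible when every stated assumption holds is a poor guide to that decision.

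**Working it through.** **Inputs.** Eligible pool 56, planned recruitment 30, drop-out about 10%, adherence 70% (Justification of sample size). Cut-offs: drop-out below 10%, adherence at least 70%, recruitment at least 50% or at least 30 (Feasibility outcome measures).

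**1. The plan's own figures reproduce.**
- 140 × 0.40 = 56, and 30/56 = 53.6%, which is just over half.
- The exact (Clopper-Pearson) 95% interval for 21/30 is 50.6% to 85.3%. Times 30, this is 15.18 to 25.58, which truncates to the stated 15 to 25.

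**2. Result exactly on plan: 30 recruited, 3 drop-outs, 21 adherent.**
- Recruitment: 30 ≥ 30, met.
- Adherence: 21/30 = 70%, met.
- Drop-out: 3/30 = 10.0%, not below 10%, missed.

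**3. Chance of meeting each cut-off when the true rate equals the planned rate (binomial).**
- Drop-out, at most 2 of 30 at 10%: 0.9^30 + 30 × 0.1 × 0.9^29 + 435 × 0.1² × 0.9^28 = 0.042 + 0.141 + 0.228 = 0.41.
- Adherence, at least 21 of 30 at 70%: 0.59.
- Recruitment, at least 30 of 56 at 53.6%: 0.55. If the cut-off is read as 50%, that is at least 28 of 56: 0.75.

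**4. Sensitivity to the planned drop-out rate, which is only approximate.**

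| True drop-out rate | P(at most 2 of 30) |
|---|---|
| 5% | 0.81 |
| 8% | 0.57 |
| 9% | 0.49 |
| 10% | 0.41 |
| 12% | 0.28 |

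**5. Criteria taken together.** Recruitment is treated as independent of the other two, and 30 patients are taken as the denominator for both.
- Drop-out and adherence independent: 0.411 × 0.589 = 0.24. With recruitment of at least 30: 0.242 × 0.554 = 0.13.
- Drop-outs counted as non-adherent, so that adherence among those retained is 0.70/0.90: the sum over k = 0, 1, 2 of P(k drop-outs) × P(at least 21 adherent of 30 − k) is 0.32. With recruitment: 0.320 × 0.554 = 0.18.
- With 28 instead of 30 as the recruitment cut-off, these become 0.18 and 0.24.
- Whatever the dependence, the joint probability cannot exceed that of the drop-out item alone: 0.41 at a true 10%.

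**6. Changing only the inequality sign.** If drop-out of exactly 10% were allowed (at most 3 of 30), that item would pass with probability 0.65, and drop-out with adherence with 0.38 (independent) to 0.46 (drop-outs non-adherent). The literal contradiction would go, but the fragility would remain.

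**The case against.** - **The planned rate is approximate.** A drop-out allowance in a sample-size paragraph is not a precise forecast. At a true 8% the item passes more often than not (0.57), and at 5% it passes with 0.81. This stands: the 0.41 belongs to a true rate of 10% and should be quoted with its sensitivity. It does not remove the conflict between the two sections, because the only rate stated is about 10%.
- **Drop-out may not be decisive.** The abstract and Aims and objectives define feasibility by recruitment, adherence and weight loss; drop-out appears only inside the recruitment item of the decision rule. But that item makes it a condition. Even without it, recruitment of at least 30 and adherence, taken as independent, pass together with probability 0.589 × 0.554 = 0.33, or 0.44 with at least 28.
- **Estimates will be reported with intervals anyway.** Statistical analysis promises point estimates with 95% confidence intervals and no p-values, and nowhere is it said that one missed item ends the programme. This is fair and lowers the stakes. It does not change the rule, which refers to point estimates alone.
- **Single cut-offs are not an error in themselves.** Agreed. The fault lies in where they are placed and in the lack of any provision for a near miss.

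A reader might go further and infer that every cut-off sits at its expected value, or that the chance of a feasible verdict is only about 0.08. The documents do not support either. They state no expected rate for weight loss or data completeness. The 0.08 needs independence and an assumed true weight-loss responder rate of 60%, which gives 0.58 for at least 18 of 30. At 70% or 80% that factor would be 0.92 or 0.997.

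**Conclusion.** The point holds in a limited form. The expected drop-out (about 10%, 3 of 30) fails the required drop-out (below 10%, at most 2 of 30), so a study exactly on plan misses its own feasibility rule on this one item. At a true 10% the item is met with probability 0.41, rising to 0.49 at 9% and 0.57 at 8%.

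Recruitment and adherence are also fixed at their planned values. They pass exactly on plan, and add risk only through sampling variation (pass probabilities 0.55 and 0.59). Drop-out, adherence and recruitment of at least 30 are met jointly with probability of about 0.13 to 0.18. This assumes that the true rates equal the planned ones, that all items are required, and that recruitment is independent of the rest. No joint figure including weight loss or data completeness should be quoted.

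This should be fixed. It is not critical, because the study is uncontrolled and descriptive and no treatment comparison depends on the rule.

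**What to change.** 1. **Drop-out.** Make Justification of sample size and Feasibility outcome measures agree. Either set the drop-out cut-off above the planned 10%, or state a lower planned rate and its basis. Allowing exactly 10% would remove the literal contradiction but leave the cut-off at the planned value.
2. **Recruitment.** Make the percentage and the count agree: of 56 eligible patients, 50% is 28, and 30 is 53.6%.
3. **Decision rule.** Judge each criterion together with its exact 95% interval. State in advance an intermediate outcome, feasible with modification, for a point estimate that narrowly misses a cut-off set at the planned value. The documents do not determine where the edges of that zone should lie, so the investigators should choose and justify them before seeing data. If exact limits are used as edges, they should be applied consistently: for 3 of 30 drop-outs the exact upper limit is 26.5%, or 7.96 of 30, so 7 drop-outs would still lie inside it.

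The cost is protocol wording only, with no change to sample size, visits or data collection. The downside is that a middle result calls for judgement instead of a yes or no.

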### Intervention

As per British National Formulary, liraglutide will be injected 0.6 mg once daily, increased in steps of 1 week up to a maintenance dose of 3 mg once daily, or the maximally tolerated. If still clinically indicated at the end of study, liraglutide will be continued and followed up as per the National Health Service (NHS) standard care. This will be reported as cumulative doses of liraglutide over the study period, considering any disruption due to potential side effects. Adherence will be checked during monthly telephone follow-ups and return of empty pens via pre-paid envelopes from the participants.

### Other aspects of care

Consistent with current standard of care, all participants will be offered lifestyle advice, including on weight reduction, monitoring of hypertension, advice regarding diabetic optimization, and reduction in alcohol.

### Feasibility outcome measures

The study will be considered feasible if as follows:Recruitment rate ≥ 50% (≥ 30 patients) of those eligible (56 patients per year), drop-out rate < 10%, and data completeness ≥ 90%Adherence to medication rate ≥ 70% in the participants at the end of study [23]. Adherence will be measured by the proportion of patients who tolerate total cumulative dose of 657 mg and more of liraglutide at 1 year (minimal maintenance dose of 1.8 mg over 365 days).Weigh loss at least 5% from baseline in ≥ 60% participants at the end of study [23, 27]. Body mass change in kilograms and BMI between the baseline, at ablation, and last days of treatment with liraglutide (± 7 days) will be measured using a single set of calibrated scales using a standardized protocol.

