### Statistical analysis

Descriptive statistics will be used to summarize demographics and medical histories. The number of patients recruited over 52 weeks will be reported as a percentage of those eligible. The adherence to the medication will be reported as a proportion of patients who tolerate a total cumulative dose of 657 mg of liraglutide or more over 52-week follow-up period. The cumulative dose of liraglutide will be calculated for each participant, and mean and standard deviation for all participants will be reported. The percentage of change in weight from baseline to the end of follow-up will be calculated for each participant, and the proportion of participants who lost weight ≥ 5% and < 5% will be reported. 

For the secondary outcome measures, descriptive statistics according to the data type will be used to report at each predefined time point (baseline, before ablation, and end of follow-up). Paired *t*-test will be used to compare the changes for continuous variables such as changes in CMR measurements, biomarkers, and electroanatomic data to determine potential mechanistic changes in relation to weight loss. As this is a feasibility study, the analysis will be reported as point estimates and corresponding 95% confidence intervals to provide precision of estimates, and no *p*-values will be reported. A Kaplan–Meier curve will be constructed for time to recurrence of AF at 1 year following ablation. This will be performed in preparation for the calculation of sample size with appropriate power for the future clinical trial based on a time-to-event superiority analysis.

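### The recruitment criterion treats 50% of 56 eligible patients as 30 when it is 28, and its denominator is worded differently across sections

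*Protocol article*

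**What the plan says.** Four sections of the Protocol article bear on the recruitment outcome.

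- **Justification of sample size** gives the planning figures: "QEHB performs first-time AF ablation on approximately 140 patients per calendar year", of whom "40% (56) of patients will be eligible for inclusion". The target follows: "We aim to recruit 30 patients in total by assuming just over 50% of eligible patients will agree to participate". Dropout is put at about 10%. The investigators expect recruitment to take no more than 52 weeks.
- **Study design and population** repeats the target: "We aim to recruit 30 patients who meet the eligibility criteria".
- **Feasibility outcome measures** turns this into a success criterion: a rate of at least 50%, equated in brackets with at least 30 "patients) of those eligible (56 patients per year".
- **Statistical analysis** says that the number recruited over 52 weeks "will be reported as a percentage of those eligible".

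In addition, the first primary objective (Aims and objectives) defines the measure as recruits divided by those eligible during the period of recruitment.

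**The concern.** The bracketed count reads as a translation of the percentage, but the two are not the same number. A feasibility criterion is meant to give one verdict on one set of data; this one can give two.

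The denominator is also unsettled. It could be the patients eligible while recruitment is open, those eligible over 52 weeks, or the forecast of 56. These coincide only if recruitment runs for exactly a year and the forecast is right.

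Recruitment is the first primary feasibility outcome, and the Background says that the definitive trial cannot be designed without knowing that recruitment rates are sufficient. An uptake figure whose denominator is open to choice is a poor basis for that trial's size and duration.

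**Working it through.** **Inputs.** From Justification of sample size: 140 first-time ablations a year, 40% eligible, target 30, dropout about 10%. From Feasibility outcome measures: at least 50%, at least 30, 56 a year.

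**1. The plan's own figures.** 140 × 0.40 = 56, as stated. 30/56 = 53.6%, which fits the sample-size wording that just over half will agree. As a planning target, 30 therefore reproduces.

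**2. The threshold.** 0.50 × 56 = 28, not 30. The three results around the boundary are:

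| Recruits of 56 | Rate | At least 50%? | At least 30? |
|---|---|---|---|
| 28 | 50.0% | yes | no |
| 29 | 51.8% | yes | no |
| 30 | 53.6% | yes | yes |

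**3. Does dropout explain the difference?** No. Inflating 28 for 10% dropout gives 28/0.9 = 31.1, so 32. Working back from the target, 30 × 0.9 = 27.

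**4. How often the two forms would disagree.** Take the number recruited as binomial with n = 56 and uptake p. The disagreement probability is P(28) + P(29), which equals P(at least 28) − P(at least 30).

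| True uptake p | P(at least 28) | P(at least 30) | Disagree |
|---|---|---|---|
| 50% | 0.55 | 0.34 | 0.21 |
| 53.6% | 0.75 | 0.55 | 0.19 |
| 60% | 0.95 | 0.87 | 0.08 |

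**5. If the number eligible is not 56.** The smallest count reaching 50% equals 30 only when 59 or 60 patients are eligible. The 56 is a forecast, so two other values are shown as illustrations:

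- 50 eligible: 25 recruits give 50% but miss the count by 5.
- 70 eligible: 30 recruits meet the count but give 30/70 = 43%; 35 would be needed for 50%.

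**6. What the denominator does.** Suppose, as an illustration, that the 30th patient is recruited at week 39 and recruitment then closes. At 56 eligible a year, 56 × 39/52 = 42 have been eligible by then.

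- Denominator as in the objectives (eligible while recruiting): 30/42 = 71%.
- Denominator of 56 as named in the criterion: 30/56 = 53.6%.

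The same recruitment experience is reported as 71% or 54% according to the section followed.

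**The case against.** The strongest reply is that the mismatch is two patients, or 3.6 percentage points, and that its origin is visible: the sample-size section assumes "We aim to recruit 30 patients in total by assuming just over 50% of eligible patients will agree to participate", and the criterion merely rounds this down to 50%. If both forms must be satisfied, the count binds at 56 eligible and there is one verdict. Both the number and the percentage will be reported, so planners of the next trial will not depend on a pass or fail at 28 or 29. The forecast of 56 is openly labelled as internal unpublished data, and nothing in the document shows it to be wrong.

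Much of this stands as to size. It does not remove the inconsistency. The sample-size wording explains why 30 was chosen, but the criterion states a threshold of 50% and presents 30 as its equivalent. Nothing says that both must be met. At the plan's own assumed uptake, about one study in five would land on the two values where the forms disagree.

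A reader might also infer that enrolment is capped at 30, so that the reported rate can never exceed 54% and uptake is understated whenever recruitment is fast. The document does not support that. It gives 30 as an aim, the criterion allows 30 or more, and no section says that recruitment closes at 30. Under the definition in the objectives, 30 recruits from 42 eligible would be reported as 71%. Even over a full year, fewer than 56 eligible patients would lift the ceiling; 30/45, for instance, is 67%. The ceiling of 53.6% applies only if enrolment stops at 30 and a denominator of 56 is used.

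**Conclusion.** The criterion is inconsistent as written. Its percentage form means 28 of 56 and its count form means 30 of 56. The two give opposite verdicts at 28 or 29 recruits, with probability about 21% at a true uptake of 50% and 19% at 53.6%. These probabilities assume exactly 56 eligible patients who decide independently. The disagreement widens if the number eligible departs from the forecast.

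The denominator is worded in three ways, and the document does not say whether recruitment ends at 30. Those two gaps leave the reported uptake open to interpretation; they do not show that it will be biased.

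The point concerns a primary feasibility outcome, but the error is small and easily removed. It is a correction worth making, not a fault that would stop the study.

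**What to change.** In Feasibility outcome measures, replace the single recruitment criterion with two:

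- **Uptake:** patients recruited divided by all patients on the screening log found eligible, from opening until recruitment closes; target at least 50%, with an exact 95% confidence interval. For scale, 30 of 56 would give 53.6% (39.7% to 67.0%).
- **Speed:** at least 30 patients recruited within 52 weeks.

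Keep 56 a year in the sample-size section as a planning assumption and remove it from the criterion. State whether recruitment closes when 30 is reached. Align the Statistical analysis section with the objectives, so that numerator and denominator cover the same period.

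The cost is a wording amendment and a screening log that records every eligible patient, including those who decline. No extra patients or visits are needed.

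### The 657 mg cumulative-dose rule does not measure adherence to 52 weeks after ablation: at 3 mg a participant can stop about 21 weeks early and still count

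*Protocol article*

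**What the plan says.** In the protocol article, Aims and objectives makes one primary objective the share of participants still adherent when the 52 weeks of post-ablation follow-up close. Justification of sample size builds on the same idea: "We expect 70% (21) of recruited participants to remain adherent to liraglutide at the end of the study". Its 95% interval of 15–25 is likewise for "recruited participants to remain adherent to liraglutide at 52 weeks following ablation".

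Feasibility outcome measures sets the threshold at 70% or more "in the participants at the end of study" and then fixes how adherence is counted: "Adherence will be measured by the proportion of patients who tolerate total cumulative dose of 657 mg and more of liraglutide at 1 year". The floor is explained there as a "minimal maintenance dose of 1.8 mg over 365 days". Statistical analysis repeats the rule as the "proportion of patients who tolerate a total cumulative dose of 657 mg of liraglutide or more over 52-week follow-up period".

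Under Intervention, the starting dose of 0.6 mg daily is "increased in steps of 1 week up to a maintenance dose of 3 mg once daily, or the maximally tolerated". That section also plans to report "cumulative doses of liraglutide over the study period, considering any disruption due to potential side effects", and it plans monthly telephone checks and the return of empty pens.

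**The concern.** The objective and the sample-size text are about persistence, meaning whether the participant is still on the drug at a given date. The counting rule is about exposure, meaning whether enough drug has been taken by then. The two agree only when the floor cannot be reached before the end date. Here the floor is built from 1.8 mg a day while the target is 3 mg a day, so most of the intended dose range passes it well before week 52. Nothing in the rule asks whether the participant is still being treated.

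This is one of the stated feasibility criteria. Background says the definitive trial cannot be designed properly without knowing that adherence holds both before and after ablation. A result of 70% could be reported, and carried into that design, although some of those counted had stopped months earlier.

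**Working it through.** **Inputs.** The floor of 657 mg, derived from 1.8 mg and 365 days (Feasibility outcome measures). The analysis window of 52 weeks = 364 days (Statistical analysis), taken as the 52 weeks after ablation because Aims and objectives describes follow-up that way. The target dose of 3 mg or the highest tolerated dose (Intervention). The expected result of 21 of 30 (Justification of sample size). By the time of ablation, at least 13 weeks into treatment, the participant is assumed to be at a steady maintenance dose.

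**The plan's own figures.** 1.8 × 365 = 657.0 mg, so the floor reproduces. The exact (Clopper–Pearson) 95% interval for 21/30 is 0.506 to 0.853, or 15.2 to 25.6 participants. This agrees with the stated 15–25, with the upper limit truncated. The arithmetic is sound, so the problem lies in the definition.

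**Day on which the floor is reached, counting from ablation.** Day reached = 657 / daily dose, rounded up. Days left = 364 − day reached.

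| Daily dose | 657 / dose | Day reached | Days left | Weeks left |
|---|---|---|---|---|
| 3.0 mg | 219 | 219 | 145 | 20.7 |
| 2.4 mg | 273.75 | 274 | 90 | 12.9 |
| 1.8 mg | 365 | not reached in 364 days | – | – |

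**The 1.8 mg case.** 1.8 × 364 = 655.2 mg, and 657 − 655.2 = 1.8 mg, which is one injection. A participant who takes every dose at the rule's own minimum is therefore classed as non-adherent over 52 weeks.

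**Effect on the criterion.** The document gives no rate of late stopping, so the effect on the proportion cannot be estimated. As an illustration only, suppose exactly 21 of 30 reach the floor (70.0%) and one of them then stops. On treatment at week 52 there are 20/30 = 66.7%, below the threshold, while the criterion still reads 70.0%. If nobody stops late, there is no effect.

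**The case against.** The best defence is that a cumulative-dose floor is a declared and reasonable choice. The drug may be given at the highest tolerated dose, interruptions for side effects are expected, and an exposure total tolerates them, whereas a status at one date would reclassify someone who stopped shortly before week 52. That stands as a reason to keep the floor. It does not turn the floor into a measure of adherence to week 52, which is what the objective and the 21-of-30 expectation describe. It also follows that passing on about 60% of the full 3 mg dose (657 / (364 × 3) = 657 / 1092 = 60.2%) is no fault in itself, since it is simply 1.8/3.

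A second defence is that late stopping would be visible anyway, through the monthly calls, the returned pens and the planned mean and standard deviation of cumulative dose. Those data would help the investigators, but none of them enters the pass/fail rule.

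A reader might go further and infer that pre-ablation doses count too. With 0.6 mg weekly steps and ablation at week 13 (the step size is not stated), a 3 mg participant would have taken 7 × (0.6 + 1.2 + 1.8 + 2.4) + 63 × 3 = 231 mg by ablation. The participant would reach the floor (657 − 231) / 3 = 142 days afterwards, 222 days (about 32 weeks) early. The text does not clearly support this. Statistical analysis ties 657 mg to the 52-week follow-up, which Aims and objectives places after ablation. The whole study period is mentioned only for reporting cumulative dose. For the same reason, the documents do not support a claim that the result turns on several rival windows. What remains of the window issue is 364 against 365 days, a minor slip.

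**Conclusion.** The point holds in a limited form. The counting rule in Feasibility outcome measures and Statistical analysis does not measure the objective in Aims and objectives, and no other section adds an on-treatment requirement. Over the 52 weeks after ablation the gap is 145 days (about 21 weeks) at 3 mg and 90 days at 2.4 mg. This assumes steady dosing from ablation and no pre-ablation doses in the total. Counting those doses would widen the gap, but the document does not clearly say that they count. The mismatch between 365 and 364 days is real but affects only a participant held at exactly 1.8 mg. How many participants would stop late is unknown, so the finding is that the criterion can be met without the objective being met, not that it will be. It should be corrected, because the criterion is meant to inform the definitive trial and the correction is nearly free.

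**What to change.** In Feasibility outcome measures and Statistical analysis:

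1. Keep an exposure floor, and state that it counts doses from ablation to 52 weeks after ablation.
2. Set the floor at or below 655.2 mg (1.8 × 364), so that full compliance at 1.8 mg passes.
3. Count a participant as adherent only if the floor is met **and** liraglutide is still being taken at 52 weeks after ablation, within the 1-week data-collection window given in Timeline and timing, as shown by the planned monthly calls and pen returns.
4. Apply the 70% threshold to this combined definition.

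The cost is one status item at a contact already planned and a sentence fixing the window. The measured proportion may be lower, because early stoppers at 2.4 or 3 mg would no longer count. A floor of exactly 655.2 mg leaves a 1.8 mg participant no room for a missed injection, so a somewhat lower value may be preferred. Skipped doses above the floor would still count as adherent and would show only in the cumulative-dose summary already planned.
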